### Statistical analysis

#### Primary and secondary

The primary outcome measure, hospital survival, will be analysed by descriptive statistics per group and percentage of total. Differences in hospital survival between groups (intervention and control group) will be tested using univariate analysis (intention to treat) by means of a Chi-square test.

As a result of the cluster effect, the primary analysis using unadjusted Chi-square test might be biased. To asses for this and other cofounders a secondary, multivariable analysis will be performed using Generalized Estimating Equations (GEE). Survival will be a dependent variable, prehospital ECPR will be included as covariate. No prehospital ECPR will be the reference category. Baseline and EMS/dispatch related variables that may potentially confound the association between prehospital ECPR and outcome will be included in this model as covariate. Known potential confounders include age, gender, time to ambulance arrival on scene, low-flow time, known medical cardiovascular conditions having an increased risk of sudden cardiac arrest. If these variables produce a *p*-value < 0.2 in a univariate comparison between the two groups, they will be included in the regression model.

Secondary outcome like survival with good neurological outcome (defined as CPC 1–2) at 6 and 12 months will be analysed using a logistic mixed regression analysis for between the two groups.

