### Allocation of patient

There are four HEMS stations serving the Netherlands, situated in Groningen, Rotterdam, Amsterdam, and Nijmegen (Fig. 2) which cover the majority of the country. Before this study, HEMS crews are not routinely involved in adult OHCA cases. In this study, HEMS will be dispatched simultaneously with the emergency medical services to every witnessed OHCA involving patients suspected to be between the ages of 18 and 50 years. As ECPR will not be offered in a regional manner (as it is typical nowadays) but on a national level, we were cautious not to overwhelm the system. To limit the number of ECPR cases, we exclude patients older than 50 years. A computer-aided system will assist the dispatcher in the central dispatch centre to determining patient eligibility. In the intervention group, the HEMS will be equipped with ECPR equipment. In the control group, HEMS will also be deployed, but without ECPR equipment. This is done to prevent a second treatment effect in the ECPR group, being the assistance of the HEMS team on scene.

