**Fig. 2 Fig2:**
[figure not shown]
HEMS Region with their 20 min geographic radius. HEMS: Helicopter Emergency Medical Services

After start of the study some large dispatch centres still seemed not ready to dispatch the HEMS because of legal uncertainties. Therefore, just after start of the study, an amendation to extend the study period was filed. To prevent protocol violation, dispatch centres who weren’t ready at the start of the study were excluded until being completely ready to comply with the study protocol.

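### The primary test is an unadjusted chi-square that ignores calendar time and station in a non-randomised stepped wedge, and adjusting for both cuts power well below the stated 90%

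*Protocol article*

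**What the plan says.** Under Statistical analysis (Primary and secondary), the Protocol article says that the difference in hospital survival "will be tested using univariate analysis (intention to treat) by means of a Chi-square test". It then qualifies this: "As a result of the cluster effect, the primary analysis using unadjusted Chi-square test might be biased". The response is a secondary multivariable GEE, and the chi-square stays primary. For the GEE, "Known potential confounders include age, gender, time to ambulance arrival on scene, low-flow time, known medical cardiovascular conditions" with raised risk of sudden arrest; if they give p < 0.2 "in a univariate comparison between the two groups, they will be included in the regression model". No calendar-time, period, step or station term is named, and the clustering unit is not stated. The neurological outcome is to be analysed by logistic mixed regression, with no terms named beyond the group comparison.

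Trial design calls the study a non-randomised stepped wedge, running from the end of 2021 to the end of 2025. Allocation of patient states: "There are four HEMS stations serving the Netherlands". Training of HEMS personnel explains the phased roll-out by limited training capacity; no random order of stations is described. The text after Fig. 2 adds that dispatch centres that were not ready "at the start of the study were excluded until being completely ready to comply with the study protocol".

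Sample size gives 175 patients per arm for 90% power at alpha 0.05, says that a loss of power from the stepped wedge was anticipated, and gives a total of 390.

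**The concern.** In a stepped wedge each station moves from control to intervention, so study arm is tied to calendar time. Any change in survival over the four years that has nothing to do with prehospital ECPR enters the pooled comparison as if it were an effect, in either direction. The changing set of dispatch centres is one documented route by which case mix could shift.

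Stations also spend different shares of the study on ECPR. Differences in survival between stations therefore cancel only partly, and the chi-square variance ignores them.

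The article sees the clustering problem but does not mention time. The back-up GEE, as described, does not name the terms that would deal with it. At stake is whether the headline result can be attributed to ECPR, and whether the stated 90% power belongs to an analysis that suits the design.

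**Working it through.** **Inputs from the article.** Control survival: 30% transported for in-hospital ECPR with 26% survival, 70% not transported with 16% survival. Intervention survival: 35%, or 30% in the first 3 months. 175 per arm, 90% power, alpha 0.05 (two-sided assumed). Four stations, about 4 years.

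**Assumptions.** Fig. 3 is not shown, so the layout is assumed: five equal periods of 0.8 years, one station crossing per step, equal cell sizes. The documents give no trend for 2021–2025 and no between-station variance.

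**1. Reproducing the plan's figure.** Control survival = 0.30 × 26% + 0.70 × 16% = 19.0%. A two-proportion calculation with independent patients gives 160 per arm for 35% vs 19% (172 with continuity correction). If 10% or 15% of intervention patients fall in the learning phase, average survival is 0.90 × 35 + 0.10 × 30 = 34.5%, or 0.85 × 35 + 0.15 × 30 = 34.25%, needing 170 or 175 per arm. Power at 175 per arm is 92.4% (35%), 90.9% (34.5%) or 90.1% (34.25%). So 175 reproduces as an independent-patient size, with almost no allowance for the stepped wedge.

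**2. Time gap between arms.** Number the periods 0 to 4, with stations crossing at 1, 2, 3 and 4. The ten control cells have period sum 0 + 1 + 3 + 6 = 10, mean 1.0. The ten intervention cells have sum 10 + 9 + 7 + 4 = 30, mean 3.0. Gap = 2 × 0.8 = 1.6 years.

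**3. Chi-square under no true effect.** SE = √(2 × 0.19 × 0.81 / 175) = 0.042. With spurious difference b, type I error = Φ(−1.96 + b/SE) + Φ(−1.96 − b/SE).

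| Trend (points/year) | b = 1.6 × trend (points) | Type I error |
|---|---|---|
| 1 | 1.6 | 6.7% |
| 2 | 3.2 | 11.9% |
| 3 | 4.8 | 20.8% |

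The only trend in the article is in its Discussion: 13.7% in 2000 to 22.3% in 2009, that is 8.6 / 9 = 0.96 points per year, followed by a plateau. At that rate b = 1.5 points and the error is about 6.5%.

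**4. Simulation under no effect** (4,000 runs per scenario, 400 patients, same layout). With no trend, station variation alone (SD 0.3 or 0.5 on the logit scale) raises the chi-square error to 7.8% or 14.5%. A rise from 16% to 22% over the study, without station variation, gives a spurious 3.0 points and 12.3%. A logistic model with station and linear time terms holds the error at 4.6% to 5.3% in every scenario.

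**5. The GEE, if its clusters are the four stations.** With independence working correlation, an uncorrected sandwich, no time term and no trend, it rejects 19% to 23% of the time. Adding linear time leaves 22% to 29%: four clusters are too few for the uncorrected sandwich.

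**6. Power of the adjusted model** (Fisher information, 19% vs 34.5%, same layout).

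| Terms | N = 350 | N = 390 | N for 90% |
|---|---|---|---|
| none | 90% | 93% | 351 |
| station + linear time | 44% | 47% | 1,141 |
| station + period | 43% | 47% | 1,150 |

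Two other assumed layouts (eight periods with early crossing; fourteen quarters) give 39% to 46% at N = 390 and a need of about 1,180 to 1,470.

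**The case against.** Several stronger readings are tempting, and the article does not support them.

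- **That the GEE has no time term and only four clusters.** The confounder list is open: it is introduced by a word meaning examples, and variables related to EMS and dispatch are admitted. The clustering unit is not given, and a small-sample correction is ordinary detail for an analysis plan that is not shown. What stands is that no time or station term is named, and that the rejection rates in step 5 are conditional on station clusters and an uncorrected sandwich. If the clusters were dispatch centres or hospitals, there would be more of them, but they would not match the level at which ECPR is rolled out.
- **That error rates of 12% to 21% are to be expected.** They need trends two to three times the steepest rise that the article reports, and it says survival has since plateaued. The plateau refers to OHCA generally and does not exclude drift among refractory arrests in 2021–2025, but the larger figures are only illustrative.
- **That the pre-study absence of HEMS from adult arrests creates a time effect within the trial.** It does not follow. Allocation of patient sends HEMS to control patients as well, precisely to avoid a second treatment effect. Pre-study practice enters only the separate historical comparison.
- **That some dispatch centres contributed intervention patients only.** The article says that unready centres were held back. It does not say that any of them joined after its station had switched.
- **That station differences pass in full into the ECPR estimate.** Each station contributes to both phases, so they partly cancel.

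None of this touches the central point. The unadjusted chi-square is fixed as the primary test in the article itself, whatever an analysis plan may add.

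**Conclusion.** The concern holds for the primary test. An unadjusted chi-square is the wrong primary analysis for a non-randomised stepped wedge, because it cannot separate ECPR from calendar time and ignores station. Under the assumed layout, a trend close to the only one documented distorts the result modestly: about 1.6 points, a tenth of the planned difference of about 15.5 points, with type I error near 7%. Steeper drift would do more, and drift in the other direction would hide a benefit. For the GEE the finding is narrower: as described, it names neither of the terms needed and does not state its clustering unit.

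The larger consequence is for power. With station and time terms, 350 to 390 patients give about 43% to 47% under the assumed layout, so the 90% in Sample size belongs to an analysis that does not suit the design. These figures rest on equal cell sizes, one crossing per step and a time trend common to all stations. The real roll-out dates would change them, though the two other layouts tried gave no better power.

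**What to change.** Make the primary analysis a logistic model for survival with terms for HEMS station and calendar time (period or a smooth function), and report an adjusted risk difference with 95% CI. If GEE or a mixed model is kept, state the clustering unit and require a small-sample correction. Keep the chi-square as descriptive. Add the same station and time terms to the neurological-outcome model. If any dispatch centre contributed to one phase only, add a sensitivity analysis restricted to centres that contributed to both.

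Re-derive the power in Sample size for this model, using the actual crossing dates and expected numbers per station, and restate it.

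The wording can be changed before database lock. The model needs only the arrest date and the attending station, which the trial must know to place a patient in a phase. The real cost is precision: about 1,150 patients would be needed for 90% power under the assumed layout, which is 1,150 / 100 = 11.5 years at the article's maximum of 100 eligible patients a year. Reaching that number is unlikely, so the lower power and wider interval should be disclosed openly. Dropping the station terms and keeping only linear time would recover part of the power (55% to 68% at N = 390 across the three layouts), but would leave station differences uncontrolled.

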**Fig. 1 Fig1:**
[figure not shown]
The 10 ECPR centres with their 30 min radius

Initiating ECPR at the cardiac arrest scene could potentially overcome both problems by reducing the duration of the low-flow state and limiting thoracic compression during transport. Performing ECPR at the scene will enlarge the potential patient pool to include individuals who might not meet the criteria for in-hospital rescue therapy due to the prolonged period of low flow caused by transportation delay. With the use of the Helicopter Emergency Medical Services (HEMS), the geographic range can be extended while maintaining a short low-flow time. This perspective is the cornerstone of the ON-SCENE study.

In the Netherlands, HEMS teams consist of an anaesthesiologist or trauma surgeon, an emergency or ambulance registered nurse, and a pilot. Their primary goal is to provide specialized medical care to trauma and non-trauma patients throughout the country with an arrival at scene after approximately 11 min. Dispatching the HEMS simultaneously with the first responders after OHCA, could potentially shorten time between collaps and initiation of ECMO bloodflow which in turn could significantly improve the chance of survival compared to either conventional resuscitation without ECPR and ECPR initiated in-hospital [10].

We therefore designed and set up the ON-SCENE study to investigate the effect of equipping the HEMS with prehospital ECPR facility on hospital survival. In this HEMS setting, a nationwide coverage for prehospital ECPR in a timely manner would be achieved. The hypothesis of this study is that implementing nationwide on scene ECPR in patients with OHCA results in shorter low-flow time in comparison to regular care, which leads to improved survival rates and less neurological impairment. Despite the increased costs for delivering ECPR on scene, it is likely to be cost-effective.

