#### Other data collected

In addition to the outcome measures, the following data will be collected:Baseline variables like gender, age, comorbidity.ALS-related variables: first observed rhythm, end-tidal CO_2_ before cannulation, motor score before cannulation, signs of life, total mg of adrenaline use, use of mechanical CPR.ECPR-related variables: duration of low-flow state, MAP before transport to hospital, ECMO blood flow before transport to hospital, any complication due to ECPR.In hospital-related variables: Systolic and diastolic blood pressure at and after 12 h arrival of emergency department, lactate at and after 12 h arrival of ED, use and type of unloading device, number of days at ECMO and ventilator.

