## Discussion

This manuscript describes the design of the ON-SCENE study, being a nationwide HEMS based initiation of ECPR on the site of cardiac arrest. This study will address the question whether HEMS equipped with prehospital ECPR facility will improve outcomes for cardiac arrest patients.

OHCA continues to impose a significant social and economic health burden on society [18]. While survival of OHCA patients increased tremendously from 13.7% in 2000 to 22.3% in 2009 [19], with bystander CPR and AED use being the most important improving factors [20, 21], survival rates have plateaued since then [22].

Multiple studies have shown a strong relation between low-flow time and survival [3, 23, 24]. ECPR is proposed as a way to further improve survival rates by means of shortening the low-flow time in patients with refractory cardiac arrest. A meta-analysis analyses and multiple observation studies indicate that ECPR does indeed significantly improve outcomes [23, 25, 26] and may be considered according to the ERC Guidelines [27]. However ECPR can only have a meaningful impact if the low-flow time remains short.

The first randomized ECPR trial was the ARREST trial, which randomised OHCA patients to ECPR or standard care and found that the ECPR group had a 43% discharge survival rate compared to 7% in the standard group [28]. However, the trial was prematurely stopped after only 30 patients were included because the predefined criteria of superiority were met. The small sample size makes the external validation of the study difficult to interpret.

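### Low-flow time is listed as a confounder for the secondary survival model and the subgroup models, although the article makes it the pathway through which on-scene ECPR is meant to work

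*Protocol article*

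**What the plan says.** All references are to the protocol article.

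- **Statistical analysis, Primary and secondary.** Hospital survival "will be tested using univariate analysis (intention to treat) by means of a Chi-square test". The article grants that this unadjusted test might be biased by clustering and confounding, and adds a secondary multivariable GEE for survival. Its covariates are meant to be baseline and EMS or dispatch variables that could confound. The list reads: "Known potential confounders include age, gender, time to ambulance arrival on scene, low-flow time, known medical cardiovascular conditions". The entry rule is a p-value below 0.2 "in a univariate comparison between the two groups, they will be included in the regression model".
- **Subgroup.** Prehospital ECPR is compared by GEE with each of two control subsets, no ECPR and in-hospital ECPR, under the same modelling strategy.
- **Background, final paragraph.** The hypothesis is that on-scene ECPR "results in shorter low-flow time in comparison to regular care, which leads to improved survival rates and less neurological impairment".
- **Discussion.** ECPR is proposed to "improve survival rates by means of shortening the low-flow time in patients with refractory cardiac arrest".
- **Other data collected.** The variable is filed as "ECPR-related variables: duration of low-flow state", apart from the baseline variables.

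Nowhere is the GEE described as a direct-effect or mediation analysis.

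**The concern.** A confounder is fixed before treatment and influences both treatment and outcome. Low-flow time is settled after HEMS acts, and the intervention is designed to change it. A model that holds it constant asks what on-scene ECPR does apart from restoring flow sooner, which is not the trial's question.

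The entry rule aggravates this. Selection on a between-group difference tends to bring a mediator in when the intervention does what it should.

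The GEE is also the only survival analysis offered to correct the bias that the article concedes in its primary test. If the chi-square test were positive and the GEE null, readers would naturally conclude that confounding explained the difference, when the covariate choice could have produced the discrepancy.

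**Working it through.** **1. Reproduce the planning scenario (Sample size section).**

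- Control survival = 0.30 × 26% + 0.70 × 16% = 7.8% + 11.2% = 19%. Intervention survival is 35%.
- n per arm = [1.96·√(2·0.27·0.73) + 1.2816·√(0.35·0.65 + 0.19·0.81)]² / 0.16² = (1.231 + 0.791)² / 0.0256 ≈ 160 (two-sided 0.05, 90% power), or 172 with continuity correction.
- If 15% of intervention patients fall in the 30% learning phase (an assumed share), survival is 0.85 × 35% + 0.15 × 30% = 34.25% and n = 175.
- The stated 175 per arm therefore reproduces for the unadjusted contrast.
- Unadjusted odds ratio = (0.35/0.65) / (0.19/0.81) = 2.30.

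**2. Adjust for low-flow time, with one low-flow distribution per arm.** Logistic simulation, 175 per arm, 35% versus 19% survival, 1,500 trials per scenario, no clustering or period effect. Means, SD (15 min) and mediated share are assumptions. Unadjusted, the odds ratio is about 2.3 and power 92% to 94%.

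| Mean low-flow, intervention vs control | Share of log-odds effect mediated | Adjusted OR | Power |
|---|---|---|---|
| 35 vs 60 min | all | 1.02 | 5% |
| 35 vs 60 min | half | 1.54 | 26% |
| 35 vs 60 min | none | 2.28 | 74% |
| 35 vs 74 min | all | 1.03 | 5% |
| 35 vs 74 min | half | 1.52 | 17% |
| 35 vs 74 min | none | 2.25 | 51% |

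A separate run with full mediation at 40 vs 60 min (SD 12) gives 1.01. The rows with no mediation show the second cost: the estimate is kept, but low-flow time is so tied to treatment that the standard error grows and power falls.

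**3. Use the article's control mix.** The 74 min figure in the Discussion is the average arrest-to-flow time in the cited Dutch trial of in-hospital ECPR. It can stand for the 30% of controls assumed to receive that treatment. For the other 70%, let the mean be x min. The blended control mean is 0.3 × 74 + 0.7·x, that is 39.7 min at x = 25, 43.2 at 30, 50.2 at 40, 57.2 at 50 and 64.2 at 60. Survival is 26%, 16% and 35% as planned. Assumptions: SD 15, floor 20 min, within-group slope −0.03 log-odds per minute, 400 runs.

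| Intervention mean | x = 25 | x = 30 | x = 40 | x = 50 |
|---|---|---|---|---|
| 35 min: adjusted OR (rejection) | 2.37 (93%) | 2.19 (86%) | 1.91 (65%) | 1.55 (29%) |
| 40 min: adjusted OR (rejection) | 2.44 (95%) | 2.22 (92%) | 1.99 (81%) | 1.64 (43%) |
| 40 min: passes p<0.2 | 34% | 83% | 100% | 100% |

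Extending x to 60 takes the odds ratio down to about 1.3. Inclusion is lowest, about 27%, where the two means nearly coincide, for example 45 min against a blended 43.2 min.

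**4. Entry rule.** With a common SD, P(p<0.2) ≈ P(|Z + δ/(SD·√(2/175))| > 1.28).

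- δ = 10 min, SD 30: 10/3.21 = 3.12, so 96.7%.
- δ = 5 min: 61% at SD 30, rising to 99.97% at SD 10.
- For comparison, a genuine confounder with an assumed standardised difference of 0.10 has 0.10/√(2/175) = 0.94 and passes only 38% of the time.

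**5. Prehospital versus in-hospital ECPR (Subgroup section).** The planning figure is flow within 35 min, against 74 min on average in the cited trial: a difference of 39 min. In-hospital ECPR controls number 0.30 × 175 ≈ 52. Even with an assumed SD of 30, the standard error is 30·√(1/175 + 1/52.5) = 4.7 min, so the difference is about 8 standard errors. On these figures entry is effectively certain, and the covariate is itself the main contrast between the two groups.

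**The case against.** The strongest reply is that the damage is limited. The primary analysis is an unadjusted intention-to-treat test, and the sample size rests on it. Neurological outcome has its own mixed model, for which low-flow time is not named. All of this stands.

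A reader might also infer that the adjusted model wipes out the treatment effect and that low-flow time is almost sure to enter the overall GEE. The documents support neither as a general statement.

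- An odds ratio near 1.0 requires the whole effect to run through low-flow time and a control arm described by one distribution well above the intervention arm. The article documents no such figure for all controls. Its sample-size assumptions also give higher survival with in-hospital ECPR (26%) than without transport to an ECPR facility (16%), while flow in the cited in-hospital trial came at 74 min on average. That is not a simple dose-response in low-flow time.
- Entry depends on the difference in means. If controls without ECPR average about 25 min, the overall difference can be small and the variable may stay out.

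This does not rescue the plan. Table 1 excludes patients with ROSC within 20 min, which limits how short control times can be. In controls without ECPR, low-flow time would presumably end at ROSC or at the end of resuscitation. It would then partly encode the outcome, which is a further reason not to adjust for it.

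Finally, the 38% pass rate for a true confounder rests on an assumed imbalance and shows no resulting bias. It illustrates the rule's weakness and is not a separate finding.

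**Conclusion.** The point holds in a bounded form. The Statistical analysis section misclassifies low-flow time as a confounder, against the Background hypothesis, the Discussion and the article's own data list. The consequence falls on the secondary survival GEE and on the subgroup GEEs that inherit its strategy. A reader might take this as invalidating the primary result or the sample size; it does neither.

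Against an unadjusted odds ratio of about 2.3, the adjusted value is about 1.0 under full mediation with a 20 to 25 min difference. Under the article's 30/70 control mix it runs from about 2.4 (no attenuation) to about 1.3, with inclusion from about 27% to 100%. The ranges rest on assumed SDs, an assumed slope and unstated low-flow times in controls without ECPR, and they ignore clustering and period.

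The direction of the error is clear whenever the intervention shortens low-flow time as intended. The case is clearest for prehospital versus in-hospital ECPR. The text should be corrected before the data are analysed.

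**What to change.** 1. Remove low-flow time from the covariates of every comparative model, including the subgroup GEEs.
2. Drop the p<0.2 screen. Enter the pre-intervention variables already on the list (age, sex, time to ambulance arrival, known cardiovascular conditions) regardless of p-value.
3. Report low-flow time as an outcome of the intervention, or use it only in a separately labelled mediation analysis, with its start and end defined identically in both arms.

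The cost is a few sentences in the protocol or analysis plan, with no new data. Under the planning rates about 175 × (0.35 + 0.19) = 94.5 survivors are expected (about 93 with the 34.25% learning-curve figure), enough for a model with this short list of covariates.

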## Methods

### Trial design

This is a nationwide multicentre, prospective, interventional, non-randomised stepped wedge study that evaluates the effect of prehospital ECPR in patients with witnessed OHCA between the age of 18 and 50 years old versus conventional HEMS care without ECPR. The study started end of 2021 and is scheduled to finish by the end of 2025.

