### Statistical consideration

#### Sample size

In the intervention group, the assumption is that ECPR, being initiated within 35 min after onset of cardiac arrest, thereby would result in a hospital survival of 35%. Due to an anticipated learning curve for the HEMS crews, a longer time to cannulation can be expected. The estimation is that this will cause a decrease of survival to 30% in the first 3 months.

In the control group, we assume that 30% of the patients with refractory arrest are transported to the hospital to receive ECPR and that 70% is not transported to an ECPR facility during cardiac arrest. Assumed hospital survival with ECPR in the hospital is 26% (data from Erasmus MC, Rotterdam the Netherlands) and 16% if the patient is not transported to an ECPR facility.

With the different scenarios described above, sample size was calculated using a simulation approach (R package contrast). Anticipating a possible loss of power caused by the stepped wedge design, 175 patients will be included in each study arm to detect the survival difference in mentioned above with 90% power and alpha 0.05. In total 390 patients will be included.

By extrapolating from the Amsterdam ‘ARREST’ database, we estimate that 450 patients in a year of below 50 years will have a witnessed OHCA. Assuming that 25% will fulfil the inclusion criteria, we expect that a maximum of 100 patients a year are eligible for the study. Therefore we assume that a period of 3.5 years should be sufficient to reach the needed number of patients for our study.

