#### Subgroup

A subgroup analysis will be performed dividing the control groups: one group who received no ECPR and one group who received ECPR after transportation to the hospital. Both therapies in the control group will be compared (using GEE) with the intervention group: prehospital ECPR. Modelling strategy will be the same as described for the primary analysis.

Other a priori defined analytic subgroups are initial cardiac rhythm (shockable vs non-shockable), time to start ECMO flow (< 40 min vs ≥ 40 min) and presence of signs of life during CPR (yes vs no).

Also, historical comparison will be made. Before the ON-SCENE study, dispatch centres were not used to activate the HEMS in an adult cardiac arrest. From the Dutch ARREST database, sequential OHCA patients will be selected who fulfil the ON-SCENE Study inclusion criteria in the timeslot before start of the ON-SCENE study. Patients in which HEMS were activated will be excluded. Hospital mortality will be the primary outcome and secondary the CPC score after 6 and 12 months.

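### The secondary adjusted model keeps a known confounder only if the arms differ on it at p < 0.2, so its covariates depend on chance imbalance instead of a list fixed in advance

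*Protocol article*

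**What the plan says.** The Trial design section describes a "non-randomised stepped wedge study that evaluates the effect of prehospital ECPR". Under Statistical analysis (Primary and secondary), hospital survival is "tested using univariate analysis (intention to treat) by means of a Chi-square test". The same section concedes that "the primary analysis using unadjusted Chi-square test might be biased" and adds a secondary multivariable GEE model to deal with clustering and confounding.

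For that model it says "Known potential confounders include age, gender, time to ambulance arrival on scene, low-flow time, known medical cardiovascular conditions". It first states that potential confounders go into the model. It then makes entry conditional: those with p < 0.2 "in a univariate comparison between the two groups, they will be included in the regression model". No variable is exempt.

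The Subgroup section splits the controls into those who had in-hospital ECPR and those who had none, and compares each with the intervention group by GEE: "Modelling strategy will be the same as described for the primary analysis".

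**The concern.** The bias from leaving a covariate out depends on two things: how far the arms differ on it and how strongly it predicts survival. The filter looks only at the first, and judges it by a p-value that moves with sample size. A strong predictor with a moderate imbalance can be left out, while a weak one with a chance imbalance is put in. These variables had already been judged confounders on subject-matter grounds, and a non-significant comparison does not undo that judgement.

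In a non-randomised study this model is the only confounding adjustment that the article states for hospital survival. Its covariates are unknown until the data are seen. Because the filter is rerun for each control subgroup, two estimates meant to be read side by side may be adjusted for different variables. Precision from prognostic covariates is also lost whenever they happen to be balanced.

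**Working it through.** **Inputs from the Sample size section.** 175 per arm, 90% power, alpha 0.05 (taken as two-sided). Intervention survival is 35%, falling to 30% in the first 3 months. Among controls, 30% receive in-hospital ECPR (26% survive) and 70% are not transported to an ECPR facility (16% survive).

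**The plan's own figure.** Control survival = 0.3 × 26% + 0.7 × 16% = 7.8% + 11.2% = 19%. For 35% v 19% the standard two-proportion formula gives 160 per arm, or 172 with continuity correction. If about 10% of intervention patients fall in the learning period (an assumption), their survival is 34.5%; this needs 170 per arm, and 175 gives power 0.909. The figure of 175 is reproduced.

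**Where the filter cuts.** For a standardised covariate, the difference in means has standard error √(2/175) = 0.107 SD. Two-sided p = 0.2 corresponds to z = 1.2816, so the cut-off is 1.2816 × 0.107 = 0.137 SD. For a true imbalance d,

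P(dropped) = Φ(1.2816 − d/0.107) − Φ(−1.2816 − d/0.107).

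| True imbalance (SD) | P(dropped), 175 per arm |
|---|---|
| 0 | 80% |
| 0.10 | 62% |
| 0.12 | 56% |
| 0.15 | 45% |
| 0.20 | 28% |
| 0.30 | 6% |

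Four independent balanced covariates are all dropped with probability 0.8⁴ = 41%.

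**Subgroup comparisons.** Applying the 30/70 split to 175 controls gives about 52 and 122.
- In-hospital ECPR: cut-off 1.2816 × √(1/52 + 1/175) = 0.20 SD. A 0.20 SD imbalance is dropped 50% of the time.
- No ECPR: cut-off 1.2816 × √(1/122 + 1/175) = 0.15 SD. The same imbalance is dropped 34% of the time.

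The smaller comparison tolerates more imbalance.

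**Effect on the adjusted estimate.** This was simulated with logistic models, independent patients and no clustering. The odds ratios per SD and the imbalances are assumptions; the article gives neither.

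| Scenario | Power, always adjusted | Power, filtered |
|---|---|---|
| 1 covariate, OR 1.5, balanced | 93.5% | 93.2% |
| 1 covariate, OR 2.0, balanced | 94.2% | 92.7% |
| 4 covariates, OR 1.5, balanced | 95.3% | 93.9% |
| 4 covariates, OR 2.0, balanced | 97.6% | 94.5% |
| 4 covariates, OR 1.65, each 0.12 SD worse under ECPR | 92–93% | 87% |

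The first four rows use 35% v 19%. The last uses 34.3% v 19%, with 25 of 175 intervention patients at the lower rate: (150 × 35% + 25 × 30%)/175 = 60/175. When a 0.1 SD imbalance favours ECPR, the two approaches have nearly equal power.

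**Residual bias with no treatment effect, 0.1 SD imbalance in the same direction (mean log-OR).**

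| Covariates | Unadjusted | Filtered | Always adjusted |
|---|---|---|---|
| 1, OR 1.5 | 0.044 | 0.014 | 0.004 |
| 4, OR 1.5 | 0.152 | 0.043 | 0.002 |
| 4, OR 2.0 | 0.223 | 0.065 | 0.003 |

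Type I error of the filtered model lay between 0.043 and 0.053 in all of these runs.

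**The case against.** The best defence is that the filter errs where it matters least. Covariates it drops are mostly close to balance; at 0.30 SD only 6% are lost. It also removes most of the bias, as the last table shows, and what remains is small beside a standard error of about 0.30 for the log-OR. The largest power loss needs four strong covariates all leaning the same way; with one covariate (OR 1.65 per SD) at 0.12 SD it is 90.2% filtered v 91.7% always adjusted. All this stands, and it limits the weight of the point.

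Three stronger readings are tempting but not supported:

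- **That the primary result is compromised.** The primary test is an unadjusted chi-square, and the filter never touches it.
- **That the filter inflates false positives.** Type I error stays near 5%.
- **That the lower log-OR of the filtered model measures confounding.** With four covariates at OR 1.65 per SD and 0.12 SD imbalance, the means are about 0.83 filtered and 0.97 always adjusted. With no imbalance at all they are 0.84 and 0.97. The gap is almost wholly non-collapsibility: an odds ratio conditional on more prognostic covariates lies further from 1.

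It may also be said that an analysis plan will settle the details. The rule, however, is stated here as a rule, so a plan that follows it inherits the fault.

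**Conclusion.** The point holds as a recommendation on pre-specification of the secondary GEE and the control-subgroup GEE comparisons. The drop rates follow from the stated sample size and the p < 0.2 rule alone, treating each covariate as standardised and continuous. The consequences, roughly 0 to 6 power points and a null bias of up to about 0.05 to 0.07 log-OR, rest on assumed covariate strengths (OR 1.5 to 2.0 per SD) and imbalances (about 0.1 SD, in the same direction on four covariates for the bias figure). The firmer objection is one of principle: the model offered as the answer to confounding has covariates chosen by the data, on a criterion that ignores prognosis, and they may differ between comparisons.

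**What to change.** Replace the p < 0.2 sentence with a fixed list: age, sex, time to ambulance arrival on scene and known cardiovascular conditions enter every adjusted model, main and subgroup, whatever their between-group p-value. Any further pre-treatment covariate should be named before data lock.

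Leave low-flow time off this list. The Background section hypothesises that on-scene ECPR improves survival by shortening it, so adjusting for it would remove part of the effect under study. For the same reason it is the listed variable most likely to pass the present filter.

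The main model can carry the list: about 0.19 × 175 = 33 control survivors and 60 intervention survivors are expected, 93 in all. The in-hospital ECPR comparison is thinner, with about 52 controls and 52 × 26% ≈ 14 control survivors. Keep the same short list there so that the comparisons are adjusted alike. The cost is one sentence and a few degrees of freedom, felt most in that subgroup; no new data or patients are needed.
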